## Analysis:

Analyses will be based on linear mixed models implemented in R statistical software and Mplus v 6.12. Primary outcomes evaluation first will follow an Intention to Treat principle with all missing values presumed returned to baseline level. Planned covariates for primary outcome, change in BMI z-score, will include gender, ethnicity, and parent marital status. For models evaluating the Primary Aim, fixed effects will include coefficients for time, treatment, and time by treatment interactions. For each outcome, selection of a covariance structure for the residuals will be based on fitting different structures (e.g., compound symmetry, unstructured) and selecting the one with the lowest sample size adjusted Akaike's Information Criterion. Significance tests will focus on the treatment by time interactions.

We will conduct analyses examining patient and therapist ratings of treatment acceptability and whether participants believe that the FBT+PT or FBT components address issues that are particularly relevant to them given the level of child behavioral problems. These analyses for the Secondary Aim will be conducted using regressions comparing FBT+PT to FBT. Survival analysis will assess the effect of FBT+PT on decreased risk for treatment drop-out (defined as subject refusal to continue treatment or failing to return to treatment without notification). Planned covariates in survival models will mirror primary analyses. Exploratory analyses will include use of generalized linear mixed effects models for repeated assessments of limited categorical and binary outcomes reflecting energy balance, video tape data, parenting, feeding/lifestyle behaviors, and psychosocial factors.

A multiple-mediator model will provide a test of whether FBT+PT leads to greater changes than FBT on proposed mediators ('a' paths) and whether changes in mediators (e.g., use of praise, limit-setting, problem-

solving, self-monitoring) at the end of treatment are related to greater decreases in BMIz over time ('b' paths) (Exploratory Aim). The product of these sets of coefficients and associated standard errors will provide effects used to test statistical significance. Mplus 6.12 includes both normal theory and bootstrap methods for estimating both total indirect (all mediators) and specific indirect effects for each proposed mediator. For the moderator hypotheses tested as part of the Exploratory Aim, the models used for the primary aim will be augmented by including a coefficient for the main effect of the moderator (e.g., parent mental health, baseline general parenting style, child food-cue responsiveness) and interactions with treatment and time.

For the Ancillary study:

**Primary aim 1: To determine behavioral and psychological phenotypes of reward and inhibition at baseline in parents and children:** Latent Profile Analysis (LPA) will be used to derive empirically defined groupings of participants based on common patterns of responses to hypothesized inhibitory control (behavioral motor, emotional regulation, and memory for food), reward function (normed physiologic reactivity, self-reported reward responsiveness), and cognitive bias (attentional bias, Stroop bias) indices of risk via maximum likelihood estimation. Models will be estimated with numbers of classes determined iteratively using the Lo-Mendell-Rubin Adjusted Likelihood Ratio Test (LMRT), the Bootstrapped Likelihood Ratio Test (BLRT), Akaike information criteria (AIC), and sample size-adjusted Bayesian information criteria (BIC). In addition to these indices, each model will be evaluated using interpretability of identified conditional means to protect from spurious classes based upon nonnormal distributions.

**Primary Aim 2: To evaluate whether the behavioral and psychological phenotypes at baseline predict weight loss in both parents and children at the 6-, 12- and 24-month timepoints:** Generalized Linear Mixed Effects Model (GLMM) regressions to accommodate potentially non-normal error distributions with random intercepts will evaluate 0-, 6-, 12-, and 24-week post-treatment BMIz for parents and children. Linear and non-linear effects for changes in BMIz will be examined for inclusion using evaluation of fit for competing unconditional models. Planned covariates will be added to include age and gender. Main effect terms for the treatment types (dummy coded with guided self-help FBT as reference) will be estimated and tested as a set. The set of baseline risk profile membership scores from LPA will be examined in a series of generalized LME models to assess independent main effects on changes over time (e.g. slopes) and potential moderating effects of treatment on changes in weight (e.g. three-way interactions). Given a potentially large number of predictors proposed to assess child and parent phenotype interactions

**Exploratory aim 1: To evaluate whether the behavioral and psychological phenotypes identified at baseline in parents and children change over the measurement period and whether these changes are associated with weight loss:** We will use in GLMM to explore changes in inhibitory control functions, reward function, and cognitive bias indices for children and parents over 6-, 12-, and 24-month assessments. We will evaluate whether the set of baseline phenotype indicators are associated with observed changes in these measures with adjustment for planned covariates and corresponding baseline values separately for children and parents.

| Table 1:
Measures                                            | Instrument                                                                               | Child or
parent | Base-
line | Post-tx
(6 month) | 6 month
Follow-up | 12 month
Follow-up |
|-----------------------------------------------------------------|------------------------------------------------------------------------------------------|--------------------|---------------|----------------------|----------------------|-----------------------|
| Anthropometry                                            | Height and weight                                                                        | C, P               | X             | X                    | X                    | X                     |
| Energy Balance
Behaviors                             | Dietary Knowledge Questionnaire                                                          | C                  | X             | X                    |                      | X                     |
|                                                                 | DHQ-II                                                                                   | P                  | X             | X                    |                      | X                     |
|                                                                 | Accelerometers and actigraphy                                                            | C                  | X             | X                    |                      | X                     |
|                                                                 | Global Physical Activity Questionnaire                                      | P                  | X             | X                    |                      | X                     |
| Demographics                                             | Race, medical history, weight history                                                    | P                  | X             |                      |                      |                       |
|                                                                 | SES-Barratt Simplified Measure of Social Status
(Hollingshead modified)  | P                  | X             |                      |                      |                       |
|                                                                 | US Household Food security module                                                        | P                  | X             | X                    | X                    | X                     |
|                                                                 | Exercise Environment Questionnaire                                          | P                  | X             | X                    | X                    | X                     |
|                                                                 | Social support                                                           | C, P               | X             | X                    | X                    | X                     |
|                                                                 | CHAOS in the home                                                           | P                  | X             | X                    | X                    | X                     |
| Videotape data                                           | Mealtime feeding behaviors                                                               | C, P               | X             | X                    | X                    | X                     |
|                                                                 | Coder Impression Inventory                                                               | C, P               | X             | X                    | X                    | X                     |
|                                                                 | Mealtime Family Interaction Coding System                                   | C, P               | X             | X                    | X                    | X                     |
| Parenting                                                | Child Report of Parent Behavior Inventory                                | C                  | X             | X                    | X                    | X                     |
|                                                                 | "Getting Along with My Parent" questionnaire                                | C                  | X             | X                    | X                    | X                     |
|                                                                 | Raising Children Questionnaire                                              | P                  | X             | X                    | X                    | X                     |
|                                                                 | The Parenting Scale                                                         | P                  | X             | X                    | X                    | X                     |
|                                                                 | Parent Importance, Confidence, & Readiness
questionnaire                 | P                  | X             |                      |                      |                       |
|                                                                 | Parent self-efficacy for health-related behaviors                           | P                  | X             | X                    | X                    | X                     |
|                                                                 | Lifestyle Behavior Checklist (Confidence scale)                             | P                  | X             | X                    | X                    | X                     |
|                                                                 | Parenting Stress Index-Short form                                        | P                  | X             | X                    | X                    | X                     |
|                                                                 | Family Adaptability and Cohesion Scale IV                                                | P                  | X             | X                    | X                    | X                     |
| Feeding and
lifestyle
behaviors                  | Child Feeding Questionnaire                                                 | P                  | X             | X                    | X                    | X                     |
|                                                                 | Adult/Child Eating Behavior Questionnaire                               | P, Pc, P           | X             | X                    | X                    | X                     |
|                                                                 | Emotional Eating Scale-Child version                                        | C                  | X             | X                    | X                    | X                     |
|                                                                 | Reward-based Eating Drive-13                                                | C,P                | X             | X                    | X                    | X                     |
|                                                                 | Eating Disorder Evaluation (binge eating
questions)                      | C                  | X             | X                    | X                    | X                     |
|                                                                 | Lifestyle Behavior Checklist (Problem Scale)                                | P                  | X             | X                    | X                    | X                     |
|                                                                 | Parent Mealtime Action Scale                                                | P                  | X             | X                    | X                    | X                     |
|                                                                 | Family Eating and Activity Habits Questionnaire                             | P                  | X             | X                    | X                    | X                     |
| Psychosocial
functioning                             | PRIME MD Patient Questionnaire                                              | P                  | X             |                      |                      |                       |
|                                                                 | CES-D                                                                       | P                  | X             |                      |                      |                       |
|                                                                 | Child Behavior Checklist                                                    | P                  | X             | X                    | X                    | X                     |
|                                                                 | Pediatric Quality of Life Inventory                                      | C, P               | X             | X                    | X                    | X                     |
|                                                                 | MINI
State-trait anxiety inventory                                                    | C
C,P           | X
X        |                      |                      |                       |
| Executive
Functioning and
Cognitive
Ability  | WRAT-4                                                                                   | C,P                | X             | X                    | X                    | X                     |
|                                                                 | Barratt Impulsivity Scale                                                                | C, P               | X             | X                    | X                    | X                     |
|                                                                 | UPPS-P                                                                                   | C,P                | X             | X                    | X                    | X                     |
|                                                                 | NIH Toolbox Battery                                                                      | C,P                | X             | X                    | X                    | X                     |
|                                                                 | CVLT-Food                                                                                | C,P                | X             | X                    | X                    | X                     |
|                                                                 | Food-Stroop                                                                              | C,P                | X             | X                    | X                    | X                     |
|                                                                 | Relative Reinforcement Value of Food                                                     | C,P                | X             | X                    | X                    | X                     |
|                                                                 | Stop Signal Task                                                                         | C,P                | X             | X                    | X                    | X                     |
|                                                                 | Digit Span                                                                               | C,P                | X             | X                    | X                    | X                     |
|                                                                 | Attention Bias                                                                           | C,P                | X             | X                    | X                    | X                     |
|                                                                 | Delay Discounting                                                           | C,P                | X             | X                    | X                    | X                     |
|                                                                 | Behavior rating Inventory of Executive Functioning                                       | P,Pc               | X             | X                    | X                    | X                     |
| Biologic
Specimens                                   | Saliva Sample – genetics                                                                 | C, P               | X             |                      |                      |                       |
|                                                                 | Stool Sample - microbiome                                                                | C,P                | X             | X                    | X                    | X                     |
| Treatment
Adherence,
Drop-out,
Acceptability | Attendance (weekly assessment)                                                           | C, P               |               | X                    |                      |                       |
|                                                                 | Habit books (self-monitoring) (weekly assessment)                                        | C, P               |               | X                    |                      |                       |
|                                                                 | Behavioral adherence (developed by team)                                                 | C, P               |               | X                    | X                    | X                     |
|                                                                 | Drop-out rates                                                                           | C, P               |               | X                    | X                    | X                     |
|                                                                 | Satisfaction survey                                                                      | C, P               |               | X                    |                      |                       |

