**6. SPECIFIC AIMS**

Authoritative parenting style has been associated with decreased obesity risk in children and can modify the delivery and impact of weight control strategies, making them more effective. At this time, gold-standard treatment for childhood obesity is family-based behavioral therapy (FBT). This treatment relies on behavioral strategies and the use of praise and a positive reinforcement system to change eating and activity behaviors, but does not target other aspects of parenting. Broadening parenting instruction to include effective limit-setting behaviors, parent-child communication, and authoritative parenting may increase parents' confidence and ability to successfully make behavior changes and modify the impact of the behavioral strategies being used.

In this application, we propose to test the efficacy of a 6 month, 20-sessions, weight control program that combines traditional family-based behavioral therapy with comprehensive parenting training (FBT+PT) and compare it to traditional family-based behavioral therapy (FBT). The FBT+PT arm will incorporate more active

skills learning to increase adoption of authoritative parenting behaviors. We will recruit and randomize 160 overweight/obese children (BMI>85th percentile and <99.9th percentile) between 7 and 12 years old and their parent into a 6 month, 20-sessions FBT+PT or FBT program and follow them for 1 year post-treatment. The primary outcome is change in child body weight (BMI z-score). Our secondary aim will be to evaluate the effect of both treatments on drop-out rates, adherence, and acceptability. As an exploratory aim, we will evaluate parent and child level mediators and moderators of weight loss in each of the treatment arms in order to inform future treatment development. We will achieve the goals of this application by pursuing the following primary and secondary aims:

- **Primary aim 1:** Examine the efficacy of FBT+PT on child body weight compared to gold standard FBT. *We hypothesize that FBT+PT will show greater decreases in child body weight (BMI z-score) compared to FBT at post-treatment and 6- and 12-months post-treatment.*
- **Secondary aim 1:** Examine drop-out, treatment adherence, and acceptability in FBT+PT and FBT. We hypothesize that families randomized to FBT+PT will have lower drop-out rates, increased program adherence (including attendance, self-monitoring, use of praise), and higher ratings of acceptability.

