## 7. BACKGROUND AND SIGNIFICANCE

The current gold standard treatment for childhood obesity is family-based behavioral therapy (FBT). This program provides the basic building blocks for weight management, including behavior therapy skills and nutrition and physical activity (PA) education. Children in these programs have shown a mean BMI z-score change of -10.3% (S.D. 9.2). However, not all children respond similarly to FBT, with only about a third of children able to maintain their weight loss over a ten year period. In addition, programs are often plagued by high drop-out rates, from 20% in academic research settings to 70% in clinical settings, impacting their efficacy. Therefore, studies are needed to determine how to optimize FBT for a greater proportion of families.

Cohort studies suggest that authoritative parenting, characterized by greater warmth/attachment and firm limit-setting, is associated with better weight outcomes. This authoritative parenting style may be important because it can alter the context in which behavioral strategies are implemented, thereby making them more effective. Furthermore, the use of praise has been associated with greater weight loss in the context of FBT, while permissive parenting is associated with poorer weight loss outcomes. Current FBT relies on behavioral strategies like self-monitoring, stimulus control, and problem-solving, but offers limited instruction on parenting, focusing only on the use of praise and positive reinforcement. Adding more comprehensive parenting training (that includes limit setting strategies and parent child communication skills) to FBT may increase the effectiveness of these programs. Ultimately, parents may become more confident to deliver weight control strategies and be able to do so in a more effective manner.

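### Setting every missing BMI z-score to baseline tilts the primary comparison towards FBT+PT if more values are missing under FBT, and shrinks a true effect if missingness is equal

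*Protocol*

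**What the plan says.** Protocol section 9, Analysis, fixes the rule for the primary outcome: "Primary outcomes evaluation first will follow an Intention to Treat principle with all missing values presumed returned to baseline level". No other missing-data method for that outcome is named. The model is a linear mixed model whose "fixed effects will include coefficients for time, treatment, and time by treatment interactions", and "Significance tests will focus on the treatment by time interactions".

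Section 6 gives the primary hypothesis, that "FBT+PT will show greater decreases in child body weight (BMI z-score) compared to FBT at post-treatment and 6- and 12-months post-treatment". Under Secondary aim 1 it adds: "We hypothesize that families randomized to FBT+PT will have lower drop-out rates". It gives no size for that difference.

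Section 7 describes FBT as an effective active treatment, with a cited "mean BMI z-score change of -10.3% (S.D. 9.2"), and describes drop-out in such programmes as ranging "from 20% in academic research settings to 70% in clinical settings".

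The Analysis text defines drop-out as leaving treatment and tests it separately by survival analysis. It does not define drop-out as a missing BMI measurement.

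**The concern.** Return-to-baseline is often regarded as conservative. That is reasonable against an untreated control whose expected change is near zero. Here the comparator itself is expected to produce weight loss, so a zero is an unfavourable score in either arm. Each filled-in child pulls that arm's mean towards no benefit, and the arm with more missing values is pulled further.

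The trial expects FBT to lose more families. If that carries over to the BMI assessments, the primary test partly measures retention, and the error runs in the direction of the trial's own hypothesis. A positive primary result could then not be separated from better attendance at assessments.

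The rule also makes no distinction by reason or pattern. A child measured at 6 months and at the last follow-up, but not in between, is scored at baseline for the middle visit, even if both neighbouring values show loss.

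**Working it through.** The protocol states no alpha, power, effect size or sample-size calculation, so there is no figure of its own to reproduce.

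**Inputs from the protocol.** 160 children randomised (section 6); mean change μ = -10.3 and SD σ = 9.2, in per cent of BMI z-score (section 7); missing value = zero change (section 9).

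**Assumptions not in the protocol.** 80 per arm; two-sided 5%; the same μ and σ in both arms (no treatment effect); missingness unrelated to outcome; the size of the gap in missing BMI.

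**Formula, one visit.** With a proportion p missing and set to zero:
- mean = (1 - p)μ
- variance = (1 - p)σ² + p(1 - p)μ²
- rejection rate = Φ(z - 1.96) + Φ(-z - 1.96), where z = |difference| / SE and SE = √[(V₁ + V₂)/80].

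**20% missing in FBT+PT, 30% in FBT.** The means are 0.8 × -10.3 = -8.24 and 0.7 × -10.3 = -7.21, a spurious difference of -1.03. The variances are 84.69 and 81.53, so SE = √(166.22/80) = 1.44 and z = 0.715. The rejection rate is 11.0%.

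**20% against 40%.** The means are -8.24 and -6.18, a difference of -2.06. The variances are 84.69 and 76.25, so SE = 1.42 and z = 1.45. The rejection rate is 30.6%. For 10% against 30% the difference is again -2.06, and the rate is 29.7%.

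**20% in both arms.** The difference is 0 and the rate is 5.0%. With a true effect of -4 points (an illustration), the estimate shrinks to 0.8 × -4 = -3.2. The SE is 1.52, z = 2.10 and power is about 56%. Using only the 64 observed children per arm, SE = 9.2 × √(2/64) = 1.63, z = 2.46 and power is about 69%.

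**Closer to the planned test.** Simulation with three post-baseline visits (assumed correlation 0.7, 2,000 runs per scenario) and a 3-degree-of-freedom test in place of the treatment-by-time test gives 8-9% at 20% against 30%, and about 23% at 20% against 40%. The same test on completers stayed between 3.9% and 5.9%.

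**Sensitivity to the assumptions (single visit).**

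| Change made | Missing FBT+PT / FBT | Return-to-baseline | Observed only |
|---|---|---|---|
| μ = -5 | 20% / 30% | 7% | - |
| μ = -5 | 10% / 30% | 12% | - |
| Missingness unrelated to outcome | 10% / 30% | 30% | 5% |
| Poor responders leave, log-odds 1 per SD | 10% / 30% | 13% | 16% |
| Poor responders leave, log-odds 2 per SD | 10% / 30% | 9% | 32% |

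In the last two rows the observed-only comparison errs in the opposite direction, against FBT+PT, because FBT loses more of its poor responders.

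**The case against.** Five points can fairly be made for the plan.

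1. **The presumption might be true.** If children who leave do return to baseline, the difference is a real effect of better retention and not a false positive. The documents settle neither case. This limits any claim about size. It does not justify a fixed fill-in, because the protocol offers no support for the presumption and applies it to isolated missed visits as well.
2. **Leaving treatment is not the same as missing BMI.** Assessments are separate visits with a remote option (section 9) and payment (section 20), so families who stop treatment may still be measured. This stands: the gap in missing BMI may be smaller than the gap in treatment drop-out. However, the protocol does not say that such families will be followed.
3. **The observed-data model has its own assumption.** As the table shows, it too can be biased if poor responders leave. This stands, and it is why return-to-baseline should be kept as a sensitivity analysis.
4. **The inputs are assumed.** No gap is stated, 10% lies below the lowest drop-out rate in section 7, and the background change need not hold at every visit. This stands, so only ranges are given.
5. **The rule applies to the evaluation done first**, and an analysis plan not shown here may add others. This stands too: a reader might infer that no sensitivity analysis is planned, but the protocol does not show that. The point concerns only the rule that the protocol itself fixes.

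A reader might also infer that the rule penalises FBT by construction, or that a false-positive rate far above 5% is to be expected. The documents do not support either. The bias needs an actual difference in missing BMI, and at a 10-point gap the inflation is moderate.

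**Conclusion.** The defect stands in conditional form. Both arms are expected to lose weight, so scoring every missing BMI z-score as zero change favours whichever arm has fewer missing values, and the trial hypothesises that FBT+PT will keep more families. With equal missingness there is no inflation, but a true effect is diluted in proportion to the missing share.

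With missingness unrelated to outcome, the type I error is about 8-11% for a 10-point gap in missing BMI and about 23-31% for a 20-point gap. The lower ends come from the repeated-visit test and the upper ends from a single visit. With a mean change of -5 the single-visit figures fall to about 7% and 12%. If poor responders are the ones who leave, the inflation is smaller again. The direction follows from the protocol's own hypotheses. The size rests on the allocation, alpha, gap and missingness mechanism assumed here.

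**What to change.** In section 9, Analysis:
- Make the primary analysis the linear mixed model already planned, fitted to all observed BMI z-scores of all randomised children, with no fill-in. This is valid under missing at random.
- State that families who stop treatment are still invited to the assessments already scheduled.
- Report missing BMI by arm and visit.
- Keep return-to-baseline as a labelled sensitivity analysis, preferably by multiple imputation around the baseline value, so that filled-in values are not treated as exact measurements.

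The cost is a few sentences and no new type of data, since the assessments are already scheduled. The downside is that the primary estimate then rests on missing at random. The sensitivity analysis shows how far the conclusion depends on that assumption, but it does not test it.
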